#### 6.4 Sample Size

After enumerating the full retrospective cohort, we will randomly select eligible HIV-positive women and their HEIs for our nested cohort. For this nested cohort, our sample size will be determined by a power calculation for our primary outcome of interest—maternal retention in care 12 months after ART initiation. For this calculation (*see summary in Table 2 below*), we assume that 75% of MIPs receive services from a CFL model of interest in our selected districts, and that approximately 73% of HIV-positive mothers receiving the SOC will be retained in care at 12 months post-ART initiation (based on the most recent, first quarter 2017 data from the Malawi national program). With a two-sided alpha of 0.05, we will have 80% power to detect a programmatically meaningful 8% difference in the proportion of mothers retained in care between those who do and do not receive CFL services by enrolling 894 mothers from CFL sites and 298 mothers from SOC sites into our nested cohort (for a total of 1,192 mothers). Assuming that approximately 75% of HIV-positive mothers in SOC sites will be virologically suppressed (a weighted composite of 88% suppression among the 73% of HIV-positive mothers in care and approximately 40% suppression among the 27% of HIV-positive mothers not in care), we will have 83% power to detect a 8% difference in the proportion of HIV-suppressed mothers between those who do and do not receive CFL services. Finally, assuming that we will enrol about one HEI for every mother in the nested cohort, and that 92% of all HEIs not receiving CFL services (i.e. receiving SOC) are alive and HIV-free at 12 months (based on published data that 7% of HEIs become HIV-infected by 12-months and 96% of HIV-exposed but *uninfected* infants are alive at 12 months), we will have 90%

power to detect a 5% difference in HIV-free survival between HEIs who do and do not receive CFL models of interest by recruiting 1,192 total HEIs..

| Table 2: Summary of power and sample size calculations for primary outcomes of interest. |                                 |                    |              |                                 |                                 |

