follow-up (LTFU) to the national PMTCT/ART program (defined by the MOH as all those who have not returned to the clinic for more than 2 months after the date when they were expected to run out of antiretrovirals and are not documented as having transferred out, stopped ART, or died); 2) mortality is 30% among HIV-infected mothers who are LTFU; and 3) a coefficient of variation of 0.15 should be adequate to obtain relatively conservative projections of precision in each joint stratum. Applying these considerations to our MIP target population, we will select between 66% and 100% of high-volume sites and about 30 MIPs at each site from across the 20 joint strata to enrol our nested cohort (**Table 3**).

**Table 3:** Illustrative sampling approach for individual mother-infant pairs at facility catchment area level.

| Joint stratum number | Total high-volume catchment areas in strata | Expected catchment areas sampled (66 - 100%) | Expected Range of number of PMTCT mothers available for sampling per joint stratum | Approximate Total Mothers sampled | Approximate Mothers with complete routine care data (.73 SOC, .80 CFLs) | Approximate Mothers Needing Tracing (0.27 SOC, 0.20 CFLs) |
|----------------------|---------------------------------------------|----------------------------------------------|------------------------------------------------------------------------------------|-----------------------------------|-------------------------------------------------------------------------|-----------------------------------------------------------|
| 1*                   | 0                                           | 0                                            | 0                                                                                  | 0                                 | 0                                                                       | 0                                                         |
| 2                    | 0                                           | 0                                            | 0                                                                                  | 0                                 | 0                                                                       | 0                                                         |

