All estimates will be corrected based on the outcomes of sampled MIPs using methods established for general HIV programs. The weights for outcomes of interest will be derived from the product of the inverse probability of sampling for the facility catchment area ( $1/[0.25]$ ), and the inverse probability of sampling for the MIP (between  $1/[80/100]$  and  $1/[10/100]$  depending on the final enumeration cohort), and the inverse probability of participation given that a MIP was sampled ( $1/[P(R = 1 | W = w)]$ ).

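### The power in Section 6.4 and Table 2 assumes equally weighted mothers, while Section 7.2.2.1 weights every estimate; on the same nested-cohort basis the stated 0.80 for retention becomes about 0.73–0.77

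*Protocol*

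**What the plan says.** **Power.** Section 6.4 sizes the nested cohort on maternal retention. It assumes "approximately 73% of HIV-positive mothers receiving the SOC will be retained in care at 12 months post-ART initiation" and, for allocation, "we assume that 75% of MIPs receive services from a CFL model of interest in our selected districts". It then states: "With a two-sided alpha of 0.05, we will have 80% power to detect a programmatically meaningful 8% difference", to be reached "by enrolling 894 mothers from CFL sites and 298 mothers from SOC sites into our nested cohort (for a total of 1,192 mothers". The same numbers are said to give 83% power for viral suppression (75% under SOC, 8-point difference; Table 2 shows 0.80) and 90% for infant HIV-free survival (92%, 5-point difference). Neither the section nor Table 2 mentions weighting or a design effect.

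**Analysis.** Section 7.2.2.1 states: "All estimates will be corrected based on the outcomes of sampled MIPs using methods established for general HIV programs". The weight is a product of inverse probabilities for catchment area, mother–infant pair and participation. The mother–infant part runs from 1/(80/100) = 1.25 to 1/(10/100) = 10, "depending on the final enumeration cohort".

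**Sampling.** Section 6.4.1 takes about 30 mothers per site whatever the site's volume, which it puts at roughly 15% to 100% of eligible mothers. It selects 66–100% of high-volume sites and says that the weights differ between joint strata. Table 3 lists, by stratum, the mothers available and the mothers sampled.

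**The concern.** The power calculation and the planned analysis use different estimators. A near-fixed take from sites of very different size makes the weights unequal by design. Unequal weights cost precision even with no correlation within facilities. The primary outcome is planned at exactly 80%, so there is no margin to absorb the loss.

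The loss falls almost entirely on the CFL arm. At the Table 3 midpoints, stratum 19 (Zomba, expert clients) supplies 180 of 1,020 CFL mothers (18%) but about 34% of the CFL weight, or 40% with the site factor.

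**Working it through.** **1. Reproduce the stated figures.** Inputs from Section 6.4: two-sided alpha 0.05, p1 = 0.73, p2 = 0.81, d = 0.08, ratio k = 3.

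- Pooled proportion: (0.73 + 3 × 0.81)/4 = 0.79.
- Uncorrected SOC size: [1.96 × √(1.333 × 0.79 × 0.21) + 0.842 × √(0.73 × 0.27 + 0.81 × 0.19/3)]² / 0.08² ≈ 281.1, rounded up to 282.
- Continuity correction: n/4 × [1 + √(1 + 2(1 + 1/k)/(n·d))]² = 281.1/4 × [1 + √(1 + 2.667/22.49)]² ≈ 297.5, so 298 SOC and 894 CFL.

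Power at 298/894 with this formula is 0.801 for retention, 0.826 for suppression (0.75 v 0.83) and 0.899 for infant HIV-free survival (0.92 v 0.97). These match 80%, 83% and 90%. Without the continuity correction, retention power at 298/894 is 0.822.

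**2. Weights from Table 3.** Weight = mothers available / mothers sampled, not allowed below 1. The floor is needed where the available count is below the number sampled (strata 10 and 16: low ends 100 v 150 and 50 v 90). Table 3 does not say whether the available count covers all areas in a stratum or only the sampled ones. I therefore ran it both without and with a site factor (total areas / sampled areas: 4/3 in stratum 6, 3/2 in strata 18 and 19, otherwise 1). The constant facility factor of 1/0.25 in Section 7.2.2.1 does not change relative weights.

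Midpoint CFL weights run from 1.0 (strata 10 and 16) to 1,000/180 = 5.6 (stratum 19), or 8.3 with the site factor. SOC weights are 1.33 to 1.75.

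**3. Kish factor** (1 + CV² of the weights) = N × Σnw² / (Σnw)², where n is the number of mothers sampled in a stratum and N the arm total. At midpoints:

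- CFL, no site factor: 1,020 × 11,589.7 / 2,970² = 1.34
- CFL, with site factor: 1,020 × 20,922.2 / 3,707.5² = 1.55
- SOC: 180 × 425.4 / 275² = 1.01

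The 894 CFL mothers then carry the information of about 894/1.340 = 667, or 894/1.553 = 576.

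**4. Power at 298 and 894 divided by their own Kish factors** (continuity-corrected formula of step 1):

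| Table 3 counts | Site factor | Kish CFL | Kish SOC | Retention | Suppression | Infant HIV-free survival |
|---|---|---|---|---|---|---|
| Low | no | 1.36 | 1.03 | 0.75 | 0.78 | 0.86 |
| Mid | no | 1.34 | 1.01 | 0.76 | 0.79 | 0.87 |
| High | no | 1.30 | 1.01 | 0.77 | 0.79 | 0.87 |
| Low | yes | 1.58 | 1.03 | 0.73 | 0.76 | 0.84 |
| Mid | yes | 1.55 | 1.01 | 0.74 | 0.77 | 0.85 |
| High | yes | 1.50 | 1.01 | 0.75 | 0.77 | 0.85 |

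**5. Sensitivity.** Without the continuity correction, retention falls from 0.82 to 0.78–0.79 (no site factor) or 0.76–0.77 (with it). Varying each CFL stratum between its low and high count independently, with the site factor, gives a CFL Kish factor of 1.38–1.74 and a corrected retention power of 0.72–0.76.

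**The case against.** Several objections have force.

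- **Retention is not known only from the nested sample.** The first stage abstracts 12-month retention for every eligible mother (2,740–3,720 in Table 3), and the nested results are meant to revise full-cohort estimates. If mothers with complete routine records contribute without heavy weights, weighting noise enters mainly through those who need tracing. This stands as a limit: some precision for retention may come back. It does not rescue the stated figure, because Section 6.4 bases its power on the nested cohort alone, and it does not help study-collected viral loads.
- **The inputs are soft.** Table 3 is labelled illustrative, its counts are ranges, and the floor at 1 is my choice. The Kish factor is an approximation that takes weights as unrelated to outcome. All true, but the 1.25-to-10 range in Section 7.2.2.1 independently implies an 8-fold spread in mother-level weights.
- **The size depends on the formula.** Without the continuity correction and without the site factor, retention is only 1–2 points below 80%. That stands, though the corrected version is the one that yields 298/894.
- **Other gaps are larger.** Clustering is ignored here, and the SOC strata in Table 3 sum to 180 mothers, not 298. Those are separate points; settling them would not remove this one.

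A reader might also infer that the protocol planned for a coefficient of variation of the weights of 0.15 and that Table 3 contradicts it. The text does not support that. It says "a coefficient of variation of 0.15 should be adequate to obtain relatively conservative projections of precision in each joint stratum", which concerns precision within a stratum, whereas the spread computed above is between strata. Nor does that allowance enter 298/894.

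**Conclusion.** The stated power omits a loss that the protocol's own sampling and weighting scheme creates. On the nested-cohort basis of Section 6.4, with the illustrative counts in Table 3 and the Kish approximation, power is about 0.73–0.77 for retention against 0.80 stated (0.76–0.79 against 0.82 without the continuity correction). It is 0.76–0.79 for suppression against 0.83 in the text and 0.80 in Table 2, and 0.84–0.87 for infant HIV-free survival against 0.90.

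These figures correct the stated calculation; they do not forecast the study's true power. A reader might infer that the study will have 73–77% power for retention. The documents do not support that: clustering, participation weights and fewer SOC mothers would lower it, while first-stage data may raise it for retention, and the protocol gives no figures to net these out.

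Nor does it follow that the weights should be dropped once site or stratum is modelled. Each joint stratum is a district crossed with a model, so such terms would absorb the CFL–SOC contrast. Stabilising weights by arm only rescales them within the arm and leaves the Kish factor unchanged.

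**What to change.** In Section 6.4 and Table 2, restate the power for all three outcomes using effective sample sizes by arm: n divided by (1 + CV² of the planned weights). Do this in a single calculation with the clustering allowance and the SOC/CFL allocation that Table 3 actually plans, since adjusting for weights alone would still not describe the design. State whether the counts in Table 3 refer to all areas in a stratum or only the sampled ones, because that decides whether the site factor applies. Add a sentence that first-stage full-cohort data may recover some precision for retention, and that the stated power does not count on it. Keep the inverse-probability weights in Section 7.2.2.1.

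The cost is a less favourable stated power and a short recalculation. No mothers are added.

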|-------------------------------------------------------------------------------------------------|---------------------------------|--------------------|--------------|---------------------------------|---------------------------------|
| Outcome                                                                                  | Estimated % in SOC sites | Effect Size | Power | Sample Size in CFL Sites | Sample Size in SOC sites |
| Maternal 12-month retention in care                                                             | 73%                             | 8%                 | 0.80         | 894 mothers                     | 298 mothers                     |
| Maternal viral suppression                                                                      | 75%                             | 8%                 | 0.80         | 894 mothers                     | 298 mothers                     |
| Infant 12-month HIV-free survival                                                               | 92%                             | 5%                 | 0.90         | 894 infants                     | 298 infants                     |

For our qualitative and mixed methods study procedures, we have not calculated sample sizes *a priori*, as we will not be conducting statistical hypothesis testing. For IDIs with HIV-positive PMTCT clients, we will select about 60 women across all 5 districts from the approximately 1,200 mother-infant pairs in our nested cohort. For other study activities, we anticipate enrolling the following additional numbers (see section 6.5 below for further details): 1) up to about 8 facility and department in-charges (or designees) and CFL program managers from each of our 20 facility catchment areas to serve as key informants for completing CFL model surveys; 2) about 20 HIV-positive PMTCT clients for private structured observations; 3) a total sample of between about 120 and 240 participants to conduct 30 FGDs with MOH healthcare workers and CFL providers (recruiting a minimum of 4 and maximum of 8 participants per focus group); 4) approximately 10 IDIs with CFL programme site-level supervisors; 5) approximately 5 IDIs with DHMT members (1 per district); and 6) about 5 to 10 IDIs with CFL programme regional/ national managers/ leaders.

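### Power for maternal viral suppression is 83% in the text of section 6.4 but 0.80 in Table 2, for the same inputs; the table cell is the wrong one

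*Protocol*

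**What the plan says.** Protocol section 6.4 calculates power for three outcomes from one nested cohort, "enrolling 894 mothers from CFL sites and 298 mothers from SOC sites into our nested cohort". The only error rate it gives is in the retention sentence: "With a two-sided alpha of 0.05, we will have 80% power".

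For viral suppression, the text begins "Assuming that approximately 75% of HIV-positive mothers in SOC sites will be virologically suppressed". It builds that figure from 88% suppression among the 73% in care and about 40% among the 27% not in care. It then concludes: "we will have 83% power to detect a 8% difference in the proportion of HIV-suppressed mothers".

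The text refers the reader to Table 2 as the summary of these calculations. The row labelled "Maternal viral suppression" shows 75% in SOC sites, effect size 8%, power 0.80, 894 mothers in CFL sites and 298 in SOC sites.

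For the other two outcomes, text and table agree: retention is 80% and 0.80, and infant 12-month HIV-free survival is 90% and 0.90.

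**The concern.** Every input to the viral-suppression calculation is the same in both places, yet the stated power differs by 3 points. At least one figure must be wrong.

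Table 2 is also doubtful on its face. It gives retention (73% against 81%) and viral suppression (75% against 83%) the same power at the same sample sizes. The second comparison has the same difference but lies further from 50%, so its variances are smaller and its power must be higher.

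What is at stake is the accuracy of a stated operating characteristic. Viral suppression is one of only three outcomes for which power is given, and it is part of the central hypothesis in section 4.0. Anyone quoting the power for it gets a different answer from the text than from the table.

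**Working it through.** **Inputs, all from section 6.4 and Table 2**
- Two-sided alpha 0.05, so z = 1.960.
- n₀ = 298 (SOC) and n₁ = 894 (CFL), a ratio of 1:3.
- SOC viral suppression: 0.88 × 0.73 + 0.40 × 0.27 = 0.7504, stated as 75%.
- Effect of 8 percentage points upward, as the central hypothesis expects: 75% against 83%.
- Two further comparisons used to identify the method: "approximately 73% of HIV-positive mothers receiving the SOC will be retained in care at 12 months" with an 8-point effect (73% against 81%), and "92% of all HEIs not receiving CFL services (i.e. receiving SOC) are alive and HIV-free at 12 months" with a 5-point effect (92% against 97%).

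**Formula.** The protocol does not name its test, so I looked for a standard one that reproduces the undisputed figures. The pooled two-proportion z-test with continuity correction does:

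power = Φ[(d − c − z·SE₀) / SE₁], where
- d = p₁ − p₀
- c = ½(1/n₀ + 1/n₁) = 0.00224
- SE₀ = √[p̄(1 − p̄)(1/n₀ + 1/n₁)], with p̄ the weighted mean proportion
- SE₁ = √[p₀(1 − p₀)/n₀ + p₁(1 − p₁)/n₁]

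**Step 1: reproduce the undisputed figures**
- Retention: p̄ = 0.79, SE₀ = 0.02724, SE₁ = 0.02887. (0.08 − 0.00224 − 0.05340)/0.02887 = 0.844, so power = 0.801. Stated: 80% and 0.80. Solving the same formula for 80% power returns exactly 298 SOC mothers, the protocol's number.
- Infant HIV-free survival: p̄ = 0.9575, SE₀ = 0.01349, SE₁ = 0.01672. (0.05 − 0.00224 − 0.02645)/0.01672 = 1.275, so power = 0.899. Stated: 90% and 0.90.

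**Step 2: apply the same formula to viral suppression**
- p̄ = 0.81, SE₀ = 0.02624, SE₁ = 0.02805. (0.08 − 0.00224 − 0.05143)/0.02805 = 0.939, so power = 0.826.
- This rounds to the text's 83%. It is 2.6 points above the table's 0.80.
- For a power of just 0.80, the formula needs only 279 SOC mothers (3 × 279 = 837 CFL), not 298.

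**Step 3: can another method give 0.80 and still fit the other rows?**

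| Method | Retention (stated 0.80) | Viral suppression (0.83 or 0.80) | Infant survival (stated 0.90) |
|---|---|---|---|
| Pooled, continuity-corrected | 0.801 | 0.826 | 0.899 |
| Pooled, uncorrected | 0.822 | 0.846 | 0.921 |
| Arcsine | 0.814 | 0.839 | 0.921 |
| Fisher exact (simulated) | 0.815 | 0.840 | 0.916 |
| Unpooled, uncorrected | 0.791 | 0.814 | 0.849 |
| Unpooled, corrected | 0.768 | 0.792 | 0.815 |

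Only the two unpooled versions come near 0.80 for viral suppression, and they miss the infant row by 5 points or more. Reading the effect as a fall from 75% to 67% gives 0.719 with correction and 0.743 without. A one-sided uncorrected test gives 0.905. None of these rescues the table cell.

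**The case against.** The strongest reply concerns weight. Section 6.4 sizes the nested cohort on retention, and section 7.1 lists retention as the only primary outcome and viral suppression as secondary. No enrolment target, analysis or decision depends on the viral-suppression power. The table errs on the cautious side, and the stated power is at least 80% under either figure. All of this stands: the error changes nothing in the design or conduct.

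A second reply is that the listed inputs do not by themselves fix 83%. The protocol names neither the test nor a continuity correction, the 75% is approximate, and standard methods range from 0.792 to 0.846. This is also fair. The case for 83% rests on matching the method to the other two outcomes, not on the viral-suppression inputs alone. But the match is close, and no tested method gives 0.80 here while reproducing those outcomes.

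A third reply is that 0.80 might mean at least 80%. The table does not support that reading: at the same sample sizes the infant row shows 0.90, so the column reports the power achieved for each outcome, not a common floor.

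**Conclusion.** The concern holds. Section 6.4 states two powers for one calculation, and the Table 2 entry is the wrong one. Under the method that reproduces the protocol's other two powers, the value is 0.826, which rounds to the text's 83%. The table understates it by about 3 points. The wrong cell equals the retention value in the row above, so a copying slip is likely, though that is only an inference.

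The conclusion rests on an inferred test (pooled, continuity-corrected, two-sided 0.05) and on the protocol's own inputs. It treats mothers as independent, as the stated figures appear to do; clustering by site is not considered here. The practical effect is limited to the description of power for one secondary outcome.

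**What to change.** Change the power entry in the viral-suppression row of Table 2 from 0.80 to 0.83. The text of section 6.4 can stay as it is. Adding a clause that names the test and states that a continuity correction was applied would let readers reproduce all three powers.

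The cost is one table cell and, optionally, one clause. No sample size, procedure or analysis changes. If the powers are later recalculated on other assumptions, the text and the table should be updated together from the same calculation.

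### The 92% SOC infant HIV-free survival in section 6.4 does not follow from its own inputs (0.93 x 0.96 = 89.3%); at 89.3% the stated 90% power is about 77%

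*Protocol*

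**What the plan says.** Protocol section 6.4 assumes that "92% of all HEIs not receiving CFL services (i.e. receiving SOC) are alive and HIV-free at 12 months". The basis given in the same sentence has two parts: "based on published data that 7% of HEIs become HIV-infected by 12-months" and "96% of HIV-exposed but *uninfected* infants are alive at 12 months". From this it claims 90% "power to detect a 5% difference in HIV-free survival between HEIs who do and do not receive CFL models of interest", with 1,192 infants in total and about one infant per mother. Table 2 repeats the planning value in the row "Infant 12-month HIV-free survival": 92%, effect 5%, power 0.90, 894 CFL and 298 SOC infants.

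For maternal viral suppression the text of section 6.4 says "we will have 83% power to detect a 8% difference in the proportion of HIV-suppressed mothers". Table 2 gives 0.80 for the same outcome, effect and group sizes.

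Section 7.2.2.1 defines infant 12-month HIV-free survival as being alive with a negative 12-month rapid test, out of all infants in the HIV-exposed birth cohort. Section 7.1 lists this outcome as secondary.

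**The concern.** The planning value and the inputs cited for it cannot both be right. The inputs imply a lower baseline, nearer to 50%, where a binomial proportion has larger variance. A fixed 5-point difference is then harder to detect, and the stated power is too high.

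What is at stake is how the infant result will be read. HIV-free survival is part of the central hypothesis in section 4.0. A reader who takes the 90% at face value would treat a null infant comparison as fairly strong evidence against a 5-point effect. At about 77% power the chance of missing such an effect is about 23%, not 10%. The text-table difference for viral suppression is a smaller matter of the same kind: two powers are printed for one calculation.

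**Working it through.** **Inputs, all from section 6.4.** Two-sided alpha of 0.05; 298 SOC and 894 CFL; SOC planning values of 73% (retention), 75% (suppression) and 92% (infant); differences of 8, 8 and 5 points. Section 4.0 sets the direction: CFL higher than SOC.

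**Step 1: the baseline.** The 96% is stated among uninfected infants, so the product needs no independence assumption:

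P(alive and HIV-free) = P(uninfected) x P(alive given uninfected) = (1 - 0.07) x 0.96 = 0.8928.

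Plain subtraction, 100 - 7 - 4 = 89%, does not give 92% either. To reach 92%, survival among uninfected infants would have to be 0.92/0.93 = 98.9%. By contrast, the suppression planning value does follow from its inputs: 0.73 x 0.88 + 0.27 x 0.40 = 0.750.

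**Step 2: reproduce the stated powers.** The protocol names no test. The formula tried is the two-proportion z-test with continuity correction:

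power = Phi{ [ |p2 - p1| - c - 1.96 x SE0 ] / SE1 }, where
- c = 0.5 x (1/298 + 1/894) = 0.00224
- SE0 = sqrt[ pbar(1 - pbar)(1/298 + 1/894) ], with pbar the weighted mean proportion
- SE1 = sqrt[ p1(1 - p1)/298 + p2(1 - p2)/894 ]

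| Outcome | SOC vs CFL | SE0 | SE1 | Power | Stated in text | Table 2 |
|---|---|---|---|---|---|---|
| Retention | 73% vs 81% | 0.02724 | 0.02887 | 0.801 | 80% | 0.80 |
| Viral suppression | 75% vs 83% | 0.02624 | 0.02805 | 0.826 | 83% | 0.80 |
| Infant HIV-free survival | 92% vs 97% | 0.01349 | 0.01672 | 0.899 | 90% | 0.90 |

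All three powers in the text are reproduced. The one that does not match is the Table 2 cell for viral suppression.

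**Step 3: recompute at the baseline that the inputs give.** With 89.28% vs 94.28%, pbar = 0.9303, SE0 = 0.01703 and SE1 = 0.01953:

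(0.05 - 0.00224 - 1.96 x 0.01703)/0.01953 = 0.736, so power = Phi(0.736) = 0.769.

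**Step 4: dependence on the method.**

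| Two-sided variant | 92% vs 97% | 89.3% vs 94.3% |
|---|---|---|
| Continuity-corrected | 0.899 | 0.769 |
| Pooled, uncorrected | 0.921 | 0.803 |
| Arcsine | 0.921 | 0.786 |
| Fisher exact (simulated) | 0.921 | 0.792 |
| Unpooled | 0.849 | 0.726 |

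Every variant loses about 12 to 13.5 points, and none reaches 0.90 at the lower baseline.

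**Step 5: what 90% power would require.** From 89.3% with 298 and 894 infants, the detectable difference is about 5.9 points (5.7 uncorrected).

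**The case against.** The strongest reply is that little depends on this figure. Section 6.4 says the sample size is determined by maternal retention, and section 7.1 lists infant HIV-free survival as secondary. Correcting the 92% changes no enrolment number, procedure or analysis. That stands, and it limits the point to a planning value and its stated power. Table 2's title does call all three outcomes primary, but sections 6.4 and 7.1 name only maternal retention as primary.

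It is also fair that 0.77 rests on a method inferred from the stated figures. Without the continuity correction the power is 0.80, a conventional level for a secondary outcome. This widens the answer to a range but does not restore 0.90.

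Four stronger readings are tempting, and the document does not support them:

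- **That the study is undersized or must enrol more.** The infant outcome does not set the sample size.
- **That 92% is the wrong figure and 89.3% the right one.** The document shows only that the value and its inputs disagree. The sponsor may have another basis for 92%, in which case the cited inputs are what need correcting.
- **That the inputs imply a CFL value of 94.3%.** That number is the SOC baseline plus the chosen 5 points. Both inputs are used up in the SOC baseline.
- **That this error drives power well below 0.73.** Clustering by site, or the smaller SOC count in Table 3's illustrative allocation, would lower power even at 92%. Those are separate matters, and the protocol gives no intracluster correlation.

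**Conclusion.** The point holds. The 92% is inconsistent with the inputs cited for it, which give 89.3%, and the outcome definition in section 7.2.2.1 offers no reading that closes the gap. If the inputs stand, power for a 5-point difference is about 0.77 by the method that reproduces the section's text, and about 0.73 to 0.80 across other two-sided variants, against the stated 0.90. The suppression power is a separate text-table conflict (83% against 0.80), and the calculation agrees with the text.

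This rests on the stated 298 and 894 infants, one infant per mother, an unchanged 5-point difference in favour of CFL, and an individual-level comparison with no design effect, as in section 6.4. The consequence is confined to how the infant result is interpreted; the primary outcome and the sample size are unaffected.

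**What to change.** - Reconcile the 92% with its cited inputs in section 6.4 and Table 2. If the 7% and 96% stand, state 89.3% and restate the power as about 0.77 for a 5-point difference, or as 0.90 for about 5.9 points. If another source supports 92%, cite it and correct the inputs.
- Use 89.3%, not a rounded 89%, beside the 0.77. At 89% vs 94% the same formula gives 0.757, which would create a new mismatch.
- Name the test used and say whether it is continuity-corrected.
- Reconcile the viral-suppression power between the text (83%) and Table 2 (0.80); the formula gives 0.83.

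The cost is a few words and figures in section 6.4 and Table 2, with no operational change. The downside is a less favourable stated power for the infant outcome.
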